### Study enrolment

All patients who previously gave informed consent in two national registries, for dialysis patients (RENINE) and kidney transplant recipients (NOTR), are selected for enrolment. Patients with CKD stages G4-G5 will be enrolled from a cohort of non-university hospitals (Santeon). All patients eligible to the registry will be followed to assess incidence of COVID-19 after vaccination, (S)AEs and vaccination status. Data of non-vaccinated patients which will be derived from RENINE and NOTR registries serve as control. Furthermore, data on vaccination efficacy in the general population, which will be derived from the National Institute for Public Health and the Environment (RIVM), serve as a control group.

For measurement of antibodies after completion of SARS-CoV-2 vaccination we intend to include a random subset of patients with CKD stages G4-G5 (*n* = 4000), patients on dialysis (*n* = 4000), and patients after kidney transplantation (*n* = 4000) (Fig. 2). Patients older than 80 years are excluded from participation because they had priority in the Dutch national vaccination scheme over other high-risk groups. Consequently, they were vaccinated longer than 28 days ago, which is the accepted term in wherein finger-prick tests are obtained for antibody measurement.

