### Informed consent for antibody measurement at home

All patients eligible to antibody measurement at home are offered two options to give informed consent, namely a written and a digital informed consent. We invited patients to register for the study by e-mail, mail and by distribution of flyers in all participating hospitals. Patients could apply for a patient information folder being sent to their home address or they could access the information folder at the website by scanning a QR-code. The QR-code directed the patients to a digital platform where they could give a digital informed consent, signed by entering a code sent to their mobile phone. In addition, we used our study website [16] to provide online access to the digital platform where informed consent could be given. This procedure enables rapid information provision of patients with minimal effort for local health care workers in the hospitals.

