#### Analysis of primary endpoint

Incidence rates of COVID-19 within 2 years after vaccination will be reported for each study population separately and incidence rates will be compared. Primary comparisons are comparisons of COVID-19 incidence rates in vaccinated patients versus non-vaccinated patients and versus the vaccinated general population. These comparisons will be made separately for patients with CKD stages G4-G5 or on KRT. For comparison of incidence rates, we will calculate crude hazard ratios. Vaccine efficacy will be reported as 100 × (1- hazard ratio). We will calculate model adjusted hazard ratios using multivariable Cox-regression, in case of imbalance in study populations regarding relevant characteristics, such as age, sex, comorbidity, kidney replacement modality and use of immunosuppressive agents. Cause specific hazard ratios will be estimated to account for competing risk of mortality. Starting date of follow-up will be the date of second vaccination in vaccinated patients. Starting date of follow-up in non-vaccinated patients will be the same date (or +/− 7 days from date of vaccination) as date of vaccination in the matched vaccinated patients to account for changes in incidence of COVID-19 over time. Non-vaccinated patients will be censored at the day of vaccination in case they are vaccinated before the end of follow-up. The aforementioned analyses will be repeated in patients with and patients without evidence of prior infection. Among vaccinated patients, incidence rates will also be compared across the various vaccines that will be used. For this purpose, vaccinated patients with CKD stages G4-G5 or on KRT and general population again will be analysed separately.

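### Mortality is counted from the second dose with no rule for participants who consent later, so their days before consent are free of deaths by construction

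*Protocol article*

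**What the plan says.** Under Analysis of primary endpoint, the protocol article states: "Starting date of follow-up will be the date of second vaccination in vaccinated patients". For controls, "Starting date of follow-up in non-vaccinated patients will be the same date" as for the matched vaccinated patient, within 7 days. No separate date of entry into the risk set is given. The Safety section analyses (S)AEs, mortality and the graft and HLA outcomes in a similar way and compares them across patient groups.

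The Study enrolment section describes two routes into the study:

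- **Registry route.** "All patients who previously gave informed consent in two national registries, for dialysis patients (RENINE) and kidney transplant recipients (NOTR), are selected for enrolment". Of this population it says: "All patients eligible to the registry will be followed to assess incidence of COVID-19 after vaccination, (S)AEs and vaccination status". Non-vaccinated controls come from the same two registries.
- **Hospital route.** CKD G4-G5 patients come from a cohort of non-university (Santeon) hospitals. No earlier consent is described, and the timing of their consent is not stated.

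A further consent applies to the antibody subset, planned at 4000 per group: "All patients eligible to antibody measurement at home are offered two options to give informed consent, namely a written and a digital informed consent". Recruitment was by open invitation: "We invited patients to register for the study by e-mail, mail and by distribution of flyers in all participating hospitals". Patients over 80 are left out of this subset because "they were vaccinated longer than 28 days ago, which is the accepted term in wherein finger-prick tests are obtained for antibody measurement".

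Table 1 makes informed consent an inclusion criterion without separating the registry cohort from the antibody subset. The abstract gives 12,000 as the size of the followed cohort, which equals the antibody subset (3 x 4000).

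**The concern.** If a participant counts only once consent is given, and consent comes after the second dose, then nobody in that group can die between the dose and consent. Starting the clock at the dose adds those days to the denominator but can add no deaths to the numerator. The same holds for incapacity severe enough to prevent consent.

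Two results are at risk. The first is early mortality after vaccination: the missing days are those in which a vaccine-related death would be looked for, and the Discussion names detection of rare harms as an aim. The second is the comparison of mortality across patient groups. If CKD G4-G5 patients enter by later consent while dialysis and transplant patients are followed through registries, only one side of the comparison is biased.

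**Working it through.** The article gives no death rate, consent date or event calculation, so there is no stated figure to reproduce beyond 3 x 4000 = 12,000.

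**Step 1. Could entry follow the second dose?** The reason for leaving out patients over 80 is that their vaccination lay too far back for the day-28 sample. That reason is needed only if patients who had already been vaccinated could still be enrolled while the sample was feasible. Had consent always preceded dose 2, time since vaccination would not be the obstacle. The Setting section agrees: the study starts when high-risk vaccination is already under way. This is an inference, because no consent date is stated.

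**Step 2. Who is affected?**

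- Registry-followed dialysis and transplant patients: no, because consent came first.
- Antibody subset, and any outcome analysis restricted to it: yes, where consent followed dose 2.
- CKD G4-G5: possibly, because the timing is not stated.

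**Step 3. Size in affected participants.** Assume a constant death hazard λ per day, consent on day d, and a horizon of H days. Per patient vaccinated:

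- Deaths counted: exp(-λd) - exp(-λH)
- Time counted from dose 2: d·exp(-λd) + [exp(-λd) - exp(-λH)]/λ
- Ratio of estimated to true rate: deaths / time / λ

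Example with an assumed 10 deaths per 100 person-years, d = 28 and H = 730.5:

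- λ = 0.10/365.25 = 0.00027379
- Deaths: 0.99236 - 0.81873 = 0.17363
- Time: 28 x 0.99236 + 0.17363/0.00027379 = 27.8 + 634.2 = 662.0 days
- Ratio: 0.17363/662.0/0.00027379 = 0.958
- With delayed entry the time is 634.2 days and the ratio is 1.00

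Ratios over assumed death rates of 2 to 15 per 100 person-years:

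| Consent in affected participants | First 28 days | 6 months | 2 years |
|---|---|---|---|
| All at day 28 | 0 | 0.84-0.85 | 0.956-0.961 |
| Uniform over days 0-28 | 0.50 | about 0.92 | 0.978-0.981 |
| Before dose 2 | 1.00 | 1.00 | 1.00 |

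A quick check agrees: the death-free share of two years is 14/730 = 1.9% (uniform, mean 14 days) or 28/730 = 3.8% (all at day 28).

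**Step 4. Pooled cohort.** If only the CKD third is affected and all groups share one death rate, the pooled two-year ratio is 0.985-0.987 (all at day 28) or about 0.993 (uniform).

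**Step 5. Between-group comparison.** The registry groups have a ratio of 1.00, so a CKD-to-registry ratio of mortality rates is multiplied by the full figure in the Step 3 table.

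**Step 6. Deaths at stake.** In 4000 patients, 4000 x (1 - exp(-28λ)) gives about 6 deaths in 28 days at 2 per 100 person-years and about 46 at 15 per 100.

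**The case against.** The strongest reply is that the enrolment timeline is not in the text. The 28 days are a window for the finger-prick test, not a limit on consent. The invitation channels carry no dates, consent before dose 2 is not ruled out, and the schedule figure is not available here. All of this stands. It makes the size conditional, but it does not supply an entry rule for anyone who did consent later.

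A reader might infer that early mortality is understated in the whole vaccinated cohort. The documents do not support that. Dialysis and transplant patients had consented to their registries beforehand and are followed whether or not they join the antibody study.

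A reader might also infer that every questionnaire-based outcome is biased. That goes too far as well. A survivor can later report a COVID-19 episode or a non-fatal adverse event from the days before consent. Only death, and incapacity that prevents consent, are excluded by construction.

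Two further points stand. Table 3 lists mortality without a 28-day window, and over the planned two years the effect is small. An article may also leave detailed risk-set rules to an analysis plan. Here, however, the article itself states the starting date and extends similar analyses to mortality.

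**Conclusion.** The point holds in a limited form. For participants whose inclusion depends on consent given after the second dose, the stated starting date credits time in which death could not be observed. Early mortality in them is understated, and their comparison with registry-followed patients is distorted.

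The bias is large in the first month (50% or 0% of the true rate in the two scenarios) and at most about 4% of the two-year rate. Pooled over the cohort it is about 0.7-1.5% if only the CKD third is affected.

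These sizes assume a constant hazard, consent between day 0 and day 28 that is unrelated to risk, death rates of 2 to 15 per 100 person-years, and equal thirds. None of these comes from the article. The text does not establish that consent was in fact late, nor that CKD G4-G5 patients are affected. It leaves both open, and it leaves unclear which cohort supplies the mortality analysis. The correction is a cheap improvement that changes nothing for patients who consented beforehand.

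**What to change.** - State which cohort supplies the mortality analyses, and when CKD G4-G5 patients consent relative to the second dose.
- Keep the second dose as the time origin. In analyses of mortality and fatal events, let any participant whose inclusion depends on consent given after that dose enter the risk set at the consent date.
- Run dialysis and transplant mortality on the full registry cohort, not on the antibody-consented subset.
- Report mortality before consent only from registry-followed patients.
- Keep non-fatal early events that participants report retrospectively by questionnaire. Use delayed entry for these only as a sensitivity analysis, since as the main analysis it would discard early safety signals.

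**Cost.** The analysis needs recorded consent dates and an entry time in each mortality model. There is less early person-time, and if CKD G4-G5 patients do enter by later consent, their mortality before consent cannot be estimated. That limit comes from the enrolment route and should be reported as such.

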### Home based finger prick tests

Blood samples will be obtained through self-obtained sample collection by use of a home-based finger prick test. The finger prick tests will be sent by mail to all participants. Written instructions are given to apply the finger prick test and how to return the finger prick tests. This procedure enables blood sampling without further need of effort from local health care workers in the hospitals. Only hemodialysis patients were offered to contact their dialysis center, when they encounter difficulties during the blood sample collection.

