In our study we encountered the challenge to approach a large population to provide informed consent and obtain blood samples under high time pressure. We provided a variety of tools to overcome possible thresholds. First, the digital informed consent gave patients the opportunity to readily access study information and participation. An alternative option to apply for written informed consent was provided, thereby including patients that are not able to access digital platforms. Second by using a home-based finger prick test for antibody measurement, patients were not obliged to make travel expense to obtain blood samples and local health care workers were not burdened with more work during the pandemic. In addition, high-risk patient groups will not be exposed to an additional risk of contamination with SARS-CoV-2 due to extra visits to the hospitals. This strategy may attribute to a higher participation grade.

While our study has a real-life observational design, there are some relevant issues to mention which may impact the results. The reported efficacy depends on the presence of widespread contamination. If for any reason widespread contamination is halted, efficacy of vaccination might be confounded, hence less contamination will occur. The opposite could be the case in the midst of a pandemic where widespread contamination occurs. Additionally, participants are vaccinated according to the national Dutch vaccination programme, in which mRNA-1273 is predominantly administered to high-risk groups, including patients on dialysis or after kidney transplantation. Consequently, certain types of vaccines might be underrepresented. In this study we will only assess the humoral response following SARS-CoV-2 vaccination. Therefore, the immunogenicity of SARS-CoV-2 vaccination in high-risk kidney patients cannot be fully assessed.

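### The vaccinated versus non-vaccinated comparison is aligned on calendar date but names no place factor, so local incidence and local uptake can bias the hazard ratio in either direction

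*Protocol article*

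**What the plan says.** All of the following is in the protocol article.

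- **Effect measure** (Analysis of primary endpoint). Crude hazard ratios are calculated first, and "Vaccine efficacy will be reported as 100 × (1- hazard ratio").
- **Alignment** (same section). Vaccinated patients enter at the second vaccination. Non-vaccinated patients enter on the same date, give or take 7 days, "as date of vaccination in the matched vaccinated patients to account for changes in incidence of COVID-19 over time". They are censored if later vaccinated. Date is the only alignment factor described.
- **Adjustment** (same section). Adjusted estimates depend on imbalance being found: "We will calculate model adjusted hazard ratios using multivariable Cox-regression, in case of imbalance in study populations regarding relevant characteristics". The article then illustrates, in an open list, what it counts as relevant: "such as age, sex, comorbidity, kidney replacement modality and use of immunosuppressive agents".
- **Source of controls** (Study enrolment). "Data of non-vaccinated patients which will be derived from RENINE and NOTR registries serve as control". These are national registries, and no restriction by place is given. Patients with CKD G4-G5 come from one group of non-university hospitals.
- **Baseline data** (Table 2). No region, hospital or dialysis centre is listed.
- **Acknowledged limitation** (Discussion). "The reported efficacy depends on the presence of widespread contamination". This concerns the general extent of spread, not differences between places.

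**The concern.** The alignment rule exists because the chance of infection differs between dates, and a patient followed during a quiet period should not be compared with one followed during a wave. The same reasoning applies to place: on a given date, a patient in a high-incidence region is more exposed than one in a low-incidence region. In a national comparison, non-vaccinated patients come disproportionately from places where uptake is low. If those places also have higher (or lower) incidence, part of the difference between the groups reflects where the patients live.

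The conditional adjustment is unlikely to catch this as written. It is triggered by imbalance in relevant characteristics. With no place variable in Table 2, a baseline comparison of the listed variables would not reveal an imbalance by place.

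At stake is the primary efficacy estimate. The study hypothesises that kidney patients are less well protected and intends to inform vaccination policy, so a shift of several percentage points could affect how the result is read.

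**Working it through.** **No figure to reproduce.** The article gives no expected hazard ratio, no uptake, no incidence by region and no number of centres. Every input below is an assumption, so a range is shown.

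**Set-up.** Two regions of equal size. Incidence without vaccination is 1 in region L and R in region H. Uptake is p_L and p_H, with a mean of 90% throughout. The true hazard ratio is the same in both regions. Events are rare enough for a rate ratio to stand for a hazard ratio, and R is the average ratio over follow-up. Matching on date alone leaves each group's regional mix as it is.

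**Formula.** Unstratified hazard ratio = true hazard ratio × M, where

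M = [(p_L + p_H·R) / (p_L + p_H)] ÷ [((1 − p_L) + (1 − p_H)·R) / ((1 − p_L) + (1 − p_H))].

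**Main example: R = 2, uptake 95% and 85%, true efficacy 60% (hazard ratio 0.40).**

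- Uptake lower in H: M = [(0.95 + 1.70)/1.80] ÷ [(0.05 + 0.30)/0.20] = 1.472/1.75 = 0.841. Hazard ratio 0.40 × 0.841 = 0.336, so efficacy reads 66.3%.
- Uptake lower in L: M = [(0.85 + 1.90)/1.80] ÷ [(0.15 + 0.10)/0.20] = 1.528/1.25 = 1.222. Hazard ratio 0.40 × 1.222 = 0.489, so efficacy reads 51.1%.
- Uptake 90% in both: M = 1.5/1.5 = 1, and efficacy reads 60%.

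**Range for a true efficacy of 60%.**

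| R | Uptake | Lower uptake in H: M | Efficacy read | Lower uptake in L: M | Efficacy read |
|---|---|---|---|---|---|
| 1.5 | 93% / 87% | 1.242/1.325 = 0.937 | 62.5% | 1.258/1.175 = 1.071 | 57.2% |
| 2 | 95% / 85% | 1.472/1.75 = 0.841 | 66.3% | 1.528/1.25 = 1.222 | 51.1% |
| 3 | 95% / 85% | 1.944/2.5 = 0.778 | 68.9% | 2.056/1.5 = 1.370 | 45.2% |
| any | equal | 1 | 60% | 1 | 60% |

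**Dependence on the true effect.** M does not involve the true hazard ratio, so the shift in percentage points grows as true efficacy falls. With R = 2 and uptake 95%/85%, a true 50% reads 57.9% (0.50 × 0.841 = 0.421) or 38.9% (0.50 × 1.222 = 0.611).

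**Effect of stratifying.** Within region L the comparison is 0.40 × 1 against 1. Within region H it is 0.40 × R against R. Both give 0.40, so a baseline hazard stratified by region returns 60% in every row.

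**The case against.** **The article does not exclude place.** It refers to matched patients without listing the matching factors, and its covariate list is only illustrative. A fuller protocol or a statistical analysis plan may name region. This stands: the supportable statement is that place is not named, not that it has been ruled out. It does not remove the point, because the article states a specific alignment rule with a specific purpose, and that rule serves the purpose in only one dimension.

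**The bias is conditional.** Uptake and incidence must both vary by place and be associated, and the documents provide evidence of neither. A reader might infer that efficacy will be overstated. The documents do not support that: the reversed pattern understates it, and equal uptake leaves it unbiased. Over two years, regional differences may also change as waves move, which could shrink the average ratio.

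**Clustering by dialysis centre.** A reader might infer that the Cox model treats patients as independent and that the intervals are therefore too narrow. The article names no variance or interval method, and that detail is commonly left to the statistical analysis plan. The vaccinated versus non-vaccinated contrast is also little affected. In a simulation on assumed inputs (80 centres of 50 patients, log-scale SD of centre rates 0.3 or 0.5, mean uptake 90%, baseline risk 10%, hazard ratio 0.5), the true standard error of the log rate ratio was 1.01 to 1.02 times the naive one with equal uptake across centres. It was 1.04 to 1.11 times with varying uptake. The rates that "will be reported for each study population separately and incidence rates will be compared" were more sensitive (1.09 to 1.28), but only if a naive method is used. The remark that "Only hemodialysis patients were offered to contact their dialysis center" concerns help with blood sampling and says nothing about clustered infection.

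**Conclusion.** The point holds in a limited form. The plan aligns on date to deal with changing incidence but names no place factor in matching, adjustment or baseline data, so confounding by local incidence and uptake is left open for the vaccinated versus non-vaccinated hazard ratio. In the main assumed example the shift is about +6 or −9 percentage points on a true efficacy of 60%. Over the range shown, the estimate runs from 45% to 69%, and the shift is nil if uptake does not differ by place. All of these sizes rest on assumed uptake and incidence, and the direction is unknown.

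This is an improvement to the stated method and not a numerical error or contradiction in the document. Intervals that are too narrow because of centre clustering are not shown and form no part of the conclusion.

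**What to change.** For the vaccinated versus non-vaccinated comparison, stratify the Cox baseline hazard by region of the treating hospital or dialysis centre, or add region to the date matching. Do this as part of the main analysis and not only when imbalance is seen. Add region to the Table 2 variables, and report uptake and incidence by region so that readers can judge how much confounding was possible.

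**Cost.** One extra field, provided the registries and the hospital cohort hold it, which the article does not say. There is also a small loss of precision, because strata with few non-vaccinated patients contribute little. Regions should therefore be broad.

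**Not required.** Same-centre matching would be impractical. With an assumed 80 patients per centre and 90% uptake, 80 × 0.10 = 8 non-vaccinated patients would have to serve 80 × 0.90 = 72 vaccinated ones, before the 7-day window and censoring at vaccination are applied. Centre-robust intervals for group rates are a reasonable option for the statistical analysis plan.

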## Methods and analysis

### Study design

This is a prospective national observational cohort study which includes all kidney patients who were vaccinated against SARS-CoV-2 in the Dutch vaccination programme. Currently available vaccines in the Netherlands are the mRNA-1273 (Moderna), BNT162b2-mRNA (Pfizer), ChAdOx1 nCoV-19 (AstraZeneca) and Ad26.COV2.S (Janssen) vaccines [5–8]. Patients with CKD stages G4-G5 or on KRT received prioritization as medical high-risk group and predominantly received the mRNA-1273 vaccine in the Dutch vaccination programme. To assess the antibody dependent immune response after vaccination, blood samples will be collected at 28 days and at 6 months after the second vaccination with a home-based finger prick test. Antibody measurement will include both the receptor binding domain (RBD) of the spike (S) antigen and the nucleocapsid (N) antigen [15]. Combining these antibody measurements allows to distinguish a natural infection from an antibody response after S1-based vaccination.

Questionnaires will be obtained during a two-year follow-up period to assess the incidence of COVID-19 or (serious) adverse events ((S)AEs) after vaccination. The study events are demonstrated in Fig. 1. The questionnaires are shown in the supplemental materials.

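### The across-vaccine comparison has no stated calendar-time control, although the same paragraph date-aligns the non-vaccinated controls because incidence changes over time

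*Protocol article*

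**What the plan says.** All of the following is in the protocol article.

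- **Analysis of primary endpoint, main contrasts:** "Primary comparisons are comparisons of COVID-19 incidence rates in vaccinated patients versus non-vaccinated patients and versus the vaccinated general population".
- **Same section, effect measure and adjustment:** "For comparison of incidence rates, we will calculate crude hazard ratios". Then: "We will calculate model adjusted hazard ratios using multivariable Cox-regression, in case of imbalance in study populations regarding relevant characteristics". The examples given are age, sex, comorbidity, kidney replacement modality and immunosuppressive agents.
- **Same section, time origin:** vaccinated patients start at their second vaccination. Non-vaccinated patients start on the date of their matched vaccinated patient, give or take 7 days, "to account for changes in incidence of COVID-19 over time".
- **Same section, across products:** "Among vaccinated patients, incidence rates will also be compared across the various vaccines that will be used". The one design feature restated for this comparison is that "vaccinated patients with CKD stages G4-G5 or on KRT and general population again will be analysed separately".
- **Study design:** kidney patients were prioritised as a high-risk group and "predominantly received the mRNA-1273 vaccine in the Dutch vaccination programme".
- **Discussion:** the consequence drawn from programme allocation is that "certain types of vaccines might be underrepresented". The Discussion also accepts, in general terms, that reported efficacy depends on how much virus is circulating.

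**The concern.** The authors recognise that background incidence moves over calendar time and control for it in one comparison. A few sentences later they compare the same endpoint between products, with every patient's clock starting at their own second dose, and state no such control. On a time-since-dose scale, patients who started in different weeks are compared at equal follow-up time but at different points of the epidemic. If one product was used earlier than another, a difference in epidemic phase enters the product hazard ratio.

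The abstract's objective covers various types of vaccination, and the section on genotype variants intends to look at vaccine types against different strains. A product ranking from this cohort is therefore likely to be read as a result, and the key points on impact offer the efficacy data as guidance for vaccination policy.

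**Working it through.** **1. What is tied to which comparison.**

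| Element | Vaccinated vs non-vaccinated | Product vs product |
|---|---|---|
| Time origin | Second dose; control aligned within 7 days | Each patient's own second dose |
| Calendar-time control | Stated, with reason | None stated |
| Covariate adjustment | If imbalanced | Possibly the same rule; not said |
| Calendar time among named covariates | Not named | Not named |
| Baseline check that could show imbalance (Statistical considerations) | Planned | Not planned between products |
| Separation by group | Stated | Stated |

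The analyses by prior infection are said to repeat all the preceding analyses. The product sentence carries over only the separation by group.

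**2. No figure of the plan's to reproduce.** The article gives no power, incidence rate or vaccination dates by product for this comparison. Everything below rests on assumed inputs and shows only whether the effect can matter.

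**3. Simple arithmetic.** Assume identical protection and starts 8 weeks apart. Weekly incidence is 3 units in the early weeks only the earlier product covers, 1 in shared weeks, and 0.5 in the late weeks only the later product covers.

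- Over 104 weeks: earlier (96×1 + 8×3) = 120; later (96×1 + 8×0.5) = 100. Later/earlier = 100/120 = 0.83 (inverse 1.20).
- Over 26 weeks: earlier (18×1 + 8×3) = 42; later (18×1 + 8×0.5) = 22. Later/earlier = 22/42 = 0.52 (inverse 1.91).

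**4. Cox hazard ratio on time since second dose, true value 1.00.** The hazard depends on calendar day only, and the second product starts 14, 30, 60 or 90 days later. Assumed hazards per person-year, with *t* in days from the earlier product's start:

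- Flat: 0.10.
- Declining: 0.05 + 0.4·exp(−*t*/45).
- Several waves: 0.02 plus bell-shaped peaks (SD 25 days) of 0.4, 0.5, 0.9 and 0.2 at days 0, 230, 330 and 650.
- Late wave: 0.02 plus a peak of 1.5 at day 740 (SD 20 days).

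| Curve | 6 months of follow-up | 2 years of follow-up |
|---|---|---|
| Flat | 1.00 | 1.00 |
| Declining (gap 14, 30, 60, 90 days) | 0.82, 0.68, 0.51, 0.42–0.43 | 0.91, 0.83, 0.75, 0.70 |
| Several waves | 0.79 to 1.93 | 0.93 to 0.97 |
| Late wave | 1.00 | 1.54 (14 days) to about 2.5 (90 days) |

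Product shares of 50/50, 90/10 and 98/2 gave almost the same values.

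Hand check of the declining curve, 60-day gap, 2 years: the cumulative hazard of the earlier product is 0.05×2 + (0.4/365)×45 = 0.1000 + 0.0493 = 0.1493. For the later product it is 0.1000 + 0.0493×exp(−60/45) = 0.1000 + 0.0130 = 0.1130. The ratio is 0.1130/0.1493 = 0.76, against 0.75 from the full calculation.

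**5. Recipient mix, if left unadjusted.** With a risk factor of rate ratio *r* and prevalences *a* and *b*, the spurious ratio is (1 + *b*(*r*−1)) / (1 + *a*(*r*−1)). For *a* = 0.4, *b* = 0.1, *r* = 2 it is 1.1/1.4 = 0.79. For *a* = 0.3, *b* = 0.2, *r* = 1.5 it is 1.10/1.15 = 0.96. The listed covariates would deal with this where they are measured and used. They do not deal with step 4.

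**6. Precision, for scale.** Assume 200 events, of which a rarely used product has 5% (10 against 190). The 95% limits are then a factor exp(1.96·√(1/10 + 1/190)) = 1.89 either side, before any bias.

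**The case against.** A reader might infer that the across-vaccine comparison is to be run without any adjustment. The text does not support that. The rule of crude and then conditionally adjusted hazard ratios is written for comparisons of incidence rates in general, and the product sentence uses the same term with words that suggest continuation. If recipients of different products are imbalanced, the condition would be met. The covariates are given as examples, so vaccination date is not excluded. What stands against this is narrower: the rule is not tied to products, no baseline comparison between products is planned to trigger it, and calendar time is not named.

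It can also be said that the time scale for an additional comparison belongs in a full protocol or analysis plan, neither of which is shown. That carries weight for detail. But the article itself fixes the time origin, the effect measure and the calendar-time control, and states that control for only one of the comparisons its reason covers.

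Finally, no section gives vaccination dates or recipient profiles by product. The one group said to have been vaccinated earlier, those over 80, is outside the 18–80 age range. This stands, and it is why the point is conditional.

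**Conclusion.** The point holds in a limited form. As written, the plan allows product to be confounded with epidemic phase in the across-vaccine comparison, and the safeguard stated elsewhere in the paragraph is not extended to it. Two conditions are needed for bias: incidence varies during follow-up, and second-dose dates differ by product within the group analysed. The article itself takes the first for granted. It is silent on the second.

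It would be tempting to conclude that epidemic waves will be reported as vaccine differences, or to quote a figure such as 1.91 as the expected error. Neither follows. With flat incidence or equal start dates the bias is nil. With several waves over the planned two years it was 3% to 7% in the assumed example, and with a single wave near either end of follow-up it reached 0.70 or about 2.5. Neither size nor direction is established.

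The two primary comparisons are not the subject of this point, and no sample size or decision rule depends on the product comparison. It deserves correction because the study's stated objective includes the various vaccine types.

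**What to change.** State for the across-vaccine comparison, within each patient group:

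1. A Cox model with calendar time as the time scale and entry at the second dose, or a model on time since second dose stratified by calendar week of vaccination. If calendar time is the scale, add time since second dose as a time-varying covariate, so that a gap in start dates does not reappear as a gap in time since dose. Under identical protection with the hazard set by calendar day, either alignment returns a hazard ratio of 1.00 by construction.
2. Adjustment for the covariates already listed (age, sex, comorbidity, modality, immunosuppression) in all cases, not only after imbalance is found.
3. A formal comparison only between products whose vaccination dates overlap in that group, with rates reported descriptively otherwise.
4. One sentence in the Discussion naming confounding by vaccination date and by recipient, alongside under-representation.

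The cost is a change of analysis wording. Second-dose dates are already needed for the time origin. Intervals will be somewhat wider, and rarely used products may have no formal comparison.
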